## Abstract

**Background:**

There is emerging evidence that exercise training could positively impact several of the cardiovascular risk factors associated with sudden cardiac death amongst patients on haemodialysis. The primary aim of this study is to evaluate the effect of an intradialytic exercise programme on left ventricular mass.

**Method and design:**

Prospective, randomised cluster open-label blinded endpoint clinical trial in 130 patients with end stage renal disease on haemodialysis. Patients will be randomised 1:1 to either 1) minimum of 30 min continuous cycling thrice weekly during dialysis or 2) standard care. The primary outcome is change in left ventricular mass at 6 months, assessed by cardiac MRI (CMR). In order to detect a difference in LV mass of 15 g between groups at 80 % power, a sample size of 65 patients per group is required. Secondary outcome measures include abnormalities of cardiac rhythm, left ventricular volumes and ejection fraction, physical function measures, anthropometric measures, quality of life and markers of inflammation, with interim assessment for some measures at 3 months.

**Discussion:**

This study will test the hypothesis that an intradialytic programme of exercise leads to a regression in left ventricular mass, an important non-traditional cardiovascular risk factor in end stage renal disease. For the first time this will be assessed using CMR. We will also evaluate the efficacy, feasibility and safety of an intradialytic exercise programme using a number of secondary end-points. We anticipate that a positive outcome will lead to both an increased patient uptake into established intradialytic programmes and the development of new programmes nationally and internationally.

**Trial registration number:**

ISRCTN11299707 (registration date 5^th^ March 2015).

**Electronic supplementary material:**

The online version of this article (doi:10.1186/s12882-016-0294-7) contains supplementary material, which is available to authorized users.

## Background

Patients on haemodialysis (HD) have extremely high rates of cardiovascular disease (CVD) related mortality [1]. US renal data system (USRDS) data suggests it is the leading cause of mortality in prevalent HD patients, accounting for 42.3 % of all deaths [2]. There is good evidence that these excessive rates of CVD are driven by a different set of processes than in the general population and attempts to modify traditional cardiac risk factors have not improved outcomes in HD patients [3]. According to the USRDS database, up to 64 % of all cardiac mortality among HD patients is due to sudden cardiac death (SCD) or arrhythmias [4] of an order of around 100 times higher than the background population [5]. Classical atherosclerotic disease is the leading cause of myocardial ischaemia in the general population [6], but this is not the case in HD patients, who are subject to a unique set of factors that change the cardiac environment and lead to changes that alter cardiac structure and function [7]. These changes are associated with SCD among HD patients and include: abnormalities in myocardial structure and function such as left ventricular hypertrophy (LVH) which is present in 75 % of dialysis patients; interstitial fibrosis and microvascular disease; with chronic volume overload and large volume ultrafiltration during dialysis treatments also contributing to the excess burden of CVD observed [8–10]. The recurrent and frequent stresses on the heart from ultrafiltration are associated with an increase in ventricular arrhythmias [11] that associate with SCD and raised biomarkers of cardiac myocyte damage as well as being independent predictors of HD related cardiac injury [12] and ultimately myocardial fibrosis [13]. To date, efforts to address these changes and improve outcomes have concentrated on medical therapies (e.g. pharmaceutical agents and implantable cardiac defibrillators) which are yet to show positive benefits [14] and studies have also demonstrated significantly increased mortality rates in HD patients after coronary revascularisation compared to the general population confirming the differences in pathogenesis [15], and again highlighting the limitations of current treatment options for HD patients.

### The benefits of exercise for patients on haemodialysis

Exercise is not as commonly-used a therapeutic intervention in HD patients as it is in other chronic diseases, e.g. cardiac and respiratory patients, and although it is clear there are a number of potential benefits from exercise in this patient population the quality of evidence is variable and there are large gaps in the evidence base. There are several systematic reviews that summarize the potential cardiovascular benefits of exercise in HD patients, as well as the likely benefits to dialysis quality, quality of life and other health related benefits [16, 17]. Exercise interventions have been largely divided into those that occur between dialysis sessions (interdialytic exercise) and those that occur during dialysis (intradialytic exercise). Whilst there is evidence that interdialytic training may yield superior cardio-respiratory adaptations, there is also a much a higher drop-out rate from such programmes [18, 19]. Intra-dialytic exercise programmes are associated with significant improvements in cardio-respiratory reserve compared to control patients and have very good adherence rates [18].

### Cardiovascular disease, exercise and HD patients

In the general population, lifestyle changes that result in increased physical exercise lower mortality [20]. Unfortunately, HD patients are less active than even sedentary healthy people with <50 % of HD patients reporting exercising once a week and unsurprisingly, higher mortality rates have been shown in such patients [21]. Exercise training during or outside of dialysis has been shown in a number of uncontrolled and non-randomised trials to lead to significant improvements in a number of cardiovascular risk factors that predispose to SCD, both traditional and those unique to patients with end stage renal disease on HD [22–24]. These studies, however, are all limited by either small sample size, non-randomised or uncontrolled design and there are no large studies that have used cardiac MRI (CMR) to assess changes in myocardial structure and function in HD patients who undergo a structured programme of exercise.

### CMR in HD patients

The term uraemic cardiomyopathy has traditionally been given to a constellation of changes in cardiac structure and function seen in patients with end stage renal disease (ESRD) that include: left ventricular hypertrophy, left ventricular dilatation and left ventricular systolic dysfunction. All of these structural and functional changes have been shown to associate with poor cardiovascular outcomes [25, 26]. It is acknowledged that studies which have used echocardiography have limited accuracy and reproducibility in defining geometric parameters and indices of systolic and diastolic function. This may be especially true in HD patients who are subject to significant changes in cardiac filling from fluid status [27]; indeed LV mass and cavity size may be overestimated in up to 50 % of dialysis patients [28]. CMR has been shown in HD patients to be a reliable technique for LV mass measurement, with excellent intra- and inter-observer variability for end-diastolic volume, end-systolic volume and LV mass [29]. LV mass is a proven continuous variable in a graded relationship with cardiovascular risk [30], and cardiovascular outcomes improve as LV mass regresses, underlying the importance of being able to accurately quantify LV mass change in intervention studies.

Echocardiography gives only limited information about tissue characterisation, compared to CMR. The risk of nephrogenic systemic fibrosis currently precludes the administration of gadolium-based contrast agents to HD patients [31]. New native T1 mapping techniques have been shown to correlate very well with histological collagen percentage in patients with severe aortic stenosis [32] and native T1 mapping has been shown to be reproducible in patients with Fabry’s disease and amyloidosis [33, 34]. Native T1 mapping holds great promise in further defining pathogenesis and tissue characterisation in HD patients and patients with ESRD and CKD.

Whilst atheroma related arterial disease remains an important factor in patients on HD, arteriosclerosis is of at least equal importance. Arteriosclerosis is a process characterised by hypertrophy and increased collagen deposition in the medial layer of the arterial wall, with circumferential calcification, and commonly occurs in patients with ESRD and CKD [35]. This causes arterial stiffness and has been shown to independently predict cardiovascular morbidity and mortality in ESRD [36]. There is a significant amount of research examining the relationship between arterial stiffness and cardiovascular disease in patients with ESRD and CKD, with much of it derived from applanation tonometry techniques that measure aortic pulse wave velocity and measures of aortic/arterial distensibility [36–38]. More recently CMR has been used to assess aortic distensibilty and there is gathering evidence of both the importance of aortic distensibility and its relationship with the development of uraemic cardiomyopathy, as well as the validity of using CMR for its assessment [39–41].

Myocardial strain and strain rate have been shown to be early markers of contractile dysfunction in many conditions that precede declines in ejection fraction. Systolic strain and strain rates have traditionally been assessed with CMR using tissue tagging techniques [42]. Increased circumferential basal strain and strain rates and reduced longitudinal function may occur in non-diabetic CKD patients, before any other structural or functional changes are apparent; suggesting it may be a very early indicator of uraemic cardiomyopathy [43]. Whilst tissue tagging is proven to be reproducible, scan acquisition requires additional long breath-holds and analysis can be cumbersome. Newer methods of strain and strain rate analysis are now available that can assess LV strain and strain rates directly from cine images. Our group has shown that Feature Tracking has excellent reproducibility and maybe more robust than tissue tagging in acute myocardial infarction patients [44, 45]. There are currently no studies that have used CMR to assess the effects of exercise on cardiac structure and function in HD patients.

The primary aim of this study is to investigate the effects of a six month programme of intra-dialytic exercise on LV mass as assessed by CMR. We will assess other cardiac structural and functional end-points, as well as biochemical markers of acute and chronic cardiac dysfunction, anthropometric measurements and measures of physical function and quality of life. An important secondary aim is to establish whether intradialytic exercise training is associated with an increase in cardiac arrhythmia, thereby addressing one of the major safety concerns.

## Methods

### Design

The protocols described in this manuscript are quorate with the most recent study protocol for the CYCLE-HD trial (version 3 15/05/2015). This study is a prospective, randomised, open-label, blinded endpoint (PROBE) study, with cluster design. The trial was given ethical approval by the NHS Research Ethics Committee East Midlands (Northampton; REC ref: 14/EM/1190). We aim to recruit 130 patients with established renal failure on maintenance HD. The study will initially take place at three dialysis units within the East Midlands Renal Network with the provision of an intradialytic cycling programme being randomised depending upon shift pattern. This study is a fully funded National Institute for Health Research (NIHR) portfolio study ‘CYCLE-HD’ (UKCRNID 17951) and is registered with the ISCRTN registry (ISRCTN11299707).

### Randomisation

Current practice in UK dialysis centres dictates that patients dialyse in one of two cohorts, either on a Monday, Wednesday and Friday or Tuesday, Thursday and Saturday. In this study, each dialysis shift will be randomised to either continue on standard dialysis therapy (control group) (see ‘Usual Care: Haemodialysis’ below) or standard dialysis therapy plus the intervention of intradialytic exercise (exercise group). This method of randomisation was modelled by the Robertson Biostatistics Centre at the Glasgow Clinical Trials Unit and peer reviewed by the National Institute of Health Research (NIHR).

### Aims of the study

To assess the effects of a six-month intra-dialytic programme of exercise on cardiovascular structure and functionTo assess the effects of a six-month intra-dialytic programme of exercise on changes in biomarkers of cardiovascular disease and systemic inflammation, physical function, body composition and quality of life measures

Two sub-studies will:Assess the short-term arrhythmogenic potential of intradialytic exerciseAssess the reproducibility of a number of CMR parameters not previously assessed or validated in HD patients

### Primary hypothesis

A six month programme of intradialytic exercise will lead to a regression in LV mass in patients receiving maintenance HD

### Secondary hypotheses

A six-month intradialytic programme of exercise for HD patients is safe with no increase in either cardiac arrhythmias or fibrosisA six-month intradialytic programme of exercise leads to an improvement in CV indices associated with an increased CV risk and SCD including: LV function; myocardial fibrosis; LV strain; cardiac arrhythmias; autonomic dysfunction; raised biochemical markers of cardiac damage and heart failure and; systemic inflammationA six-month intradialytic programme of exercise leads to an improvement in physical function and QOL

### Outcome measures

Primary outcomes measure:LV mass in grams using CMR

Secondary outcome measures:Cardiac arrhythmias, including frequency; isolated ectopy as a percentage of the total beats on the Holter monitor record; ventricular arrhythmias stratified according to the Lown classification with classes 3 and above taken as complex; and heart rate variability. Patients undergoing exercise intervention will undergo additional 48 h recording to assess rhythm data, during and after exercise on dialysis. Interim analysis is planned to identify any potential adverse rhythm disturbances associated with exerciseLeft ventricular end-diastolic and end-systolic volumes and ejection fraction (%) using CMR and echocardiography. Measures of systolic and diastolic dysfunction and myocardial fibrosis using CMR and ECHOAortic stiffness: Aortic distensibility and/or pulse wave velocityAnthropometric measures including, but not limited to, weight, height and waist circumferencePhysical function assessed by shuttle walk tests, sit to stand tests, balance tests and gait speed (the short physical performance battery)Objective assessments of physical activity using validated questionnaires and tri-axial accelerometryQuality of life (QOL) using validated questionnairesBlood markers of inflammation, cardiovascular dysfunction and cardiovascular riskSelected clinical episodes including: all hospitalisations; all-cause mortality; cardiovascular mortality; and cardiovascular morbidity including non-fatal myocardial infarction, cerebrovascular event, critical limb ischaemia

### Participant identification and recruitment

Prevalent adult patients undergoing in-centre maintenance HD at one of the enrolled units are eligible for inclusion in the study. Full lists of inclusion and exclusion criteria are included in Table 1.

**Table 1 Tab1:** Eligibility and Exclusion criteria

Eligibility Criteria	Exclusion Criteria
• Prevalent HD patient (> three months) • Aged 18 years or older • Able and willing to give informed consent	• unable to participate in current exercise programme due to perceived physical or psychological barriers • unable to undergo MRI scanning (metal implants, severe claustrophobia) • unfit to undertake exercise according to the American College of Sports Medicine (ACSM) guidelines

Patients will be recruited from centres within the East Midlands Renal Network, which cares for approximately 820 HD patients across four Counties in the United Kingdom. The three principal centres in Leicestershire care for around 350 patients. We anticipate 80 % will meet the inclusion criteria (320 patients). Conservatively assuming a 50 % consent/participation rate this will leave approximately 160 patients from which we will need to recruit 130.

### Consent

Consent will be performed according to the rules of good clinical practice. The cluster randomisation design of this trial means that at recruitment researchers will know, based on the days on which they have dialysis, whether the patient will be in the control or the intervention group. Although it will become obvious to patients when they commence the trial whether they will be in the control group, or the intervention group, this will not be explained to patients before they consent to reduce selection bias. A copy of the consent form is included as Additional file 1.

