#### Statistical analytic approach for primary outcome

The primary outcome is the change from baseline at six months in LV mass. Change from baseline will be calculated for each subject as the value at month six minus the baseline value. Differences in primary outcome measure between the intervention groups (exercise and control) will be tested within a linear mixed model containing a covariate for the intervention group and a random effect for the cohort (centre and shift). These models may be further adjusted for any imbalances between the intervention groups with respect to the baseline characteristics. All statistical analyses will be performed by a biostatistician from the Robertson Centre for Biostatistics, University of Glasgow.

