## Discussion

The primary aim of this study is to assess the effect of a six month programme of intradialytic exercise on LV mass as assessed by CMR. The cluster randomization design was chosen for the advantages in reducing exercise contamination of the control group and to ensure demographic homogeneity. There is the possibility that this could create selection bias if patients are aware which cohorts have been randomised to intervention and control before they are enrolled, but this will be minimised by not revealing the method of randomisation to patients until after they have consented to participation *and* completed all baseline assessments. This study will provide the opportunity to evaluate the effects of a structured programme of intradialytic exercise on a number of secondary outcomes. Whilst clinical outcome data will be collected, this study is not designed to evaluate the effects of exercise on mortality.

CMR used in this study is the gold standard technique for the quantification of LV mass, volumes and function. We anticipate it will be technically challenging to obtain high quality images for some patients who may struggle to lie flat for long periods or who find breath holding difficult. The CMR protocol has been carefully designed to acquire all desired images in the most efficient way possible and have pioneered techniques that allow shorter scan times, with the primary outcome measure obtained early in case of premature scan termination. The CMR radiographers at the NIHR-Leicester Cardiovascular BRU have many years’ experience obtaining scans from patients with similar burdens of co-morbid disease [45, 76, 77]. The increased signal noise ratio obtained at 3 T allows the faster acquisition of cine images (4–5 s) for patients who are poor at breath-holding and free-breathing techniques can also be used with acceptable image quality.

There are some data suggesting interdialytic exercise may yield superior cardio-respiratory adaptations to intradialytic exercise programmes, but with significantly higher drop-out rates [18, 19]. Given the proven benefits of intradialytic exercise programmes compared to control patients and the superior adherence rates [18], pragmatically an intradialytic exercise programme was chosen as it is the most likely to be translated successfully into clinical practice.

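### Researchers know each patient's arm at recruitment and one exclusion is a judgement about exercise; the stated safeguards mask only patients, so selection through the recruiter is not addressed

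*Protocol article*

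**What the plan says.** - **Unit of allocation.** Under Randomisation, each dialysis shift is allocated as a whole to usual care or to usual care plus intradialytic cycling. Individuals are then recruited from the shifts.
- **What recruiters know.** The Consent section says of the moment when patients are enrolled: "researchers will know, based on the days on which they have dialysis, whether the patient will be in the control or the intervention group".
- **Exclusions.** Table 1 has three, the same for both arms. One covers patients who cannot have an MRI scan. The other two concern exercise: "unable to participate in current exercise programme due to perceived physical or psychological barriers" and "unfit to undertake exercise according to the American College of Sports Medicine (ACSM) guidelines".
- **Safeguards.** On the arm a patient will be in, Consent says "this will not be explained to patients before they consent to reduce selection bias". The Discussion accepts that "this could create selection bias if patients are aware which cohorts have been randomised to intervention and control before they are enrolled", and continues that "this will be minimised by not revealing the method of randomisation to patients until after they have consented to participation" and baseline assessment is complete.
- **Analysis.** The primary model has a term for intervention group and a random effect for cohort. Beyond that, "These models may be further adjusted for any imbalances between the intervention groups with respect to the baseline characteristics".

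**The concern.** When clusters are allocated first and people are selected afterwards, randomisation balances the clusters but not the people chosen from them. That balance then depends on the selector either not knowing the arm or having no discretion. Here the selector knows the arm, and at least one criterion leaves discretion.

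A patient thought frail or reluctant could be judged to face barriers on a cycling shift and be accepted on a control shift. The arms would then differ at entry in fitness or motivation. These attributes bear on the physical function, quality of life and hospitalisation outcomes, and may bear on how LV mass changes. Recruiting more patients does not shrink a bias of this kind. The article discusses selection bias only as something that arises through patients.

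**Working it through.** The point rests on setting the sections of the article against each other. There is no stated figure to reproduce.

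**Step 1: is the arm known when eligibility is judged?** The article says researchers know it at recruitment. Because it follows from dialysis days, it is known before approach wherever the shift has already been allocated. No section describes an eligibility assessor unaware of the allocation, or screening completed before shifts are allocated.

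**Step 2: is there room for discretion?**

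| Table 1 exclusion | Basis | Room for uneven application |
|---|---|---|
| Perceived barriers to the exercise programme | Judgement; whose perception counts is not stated | Yes |
| Unfit under the sports medicine guideline | External guideline | Less |
| Unable to have MRI | Implants, severe claustrophobia | Little |

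**Step 3: what does each protection reach?**

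| Protection | Patient route | Recruiter route |
|---|---|---|
| Arm not explained before consent (Consent) | Yes | No |
| Method not revealed until after consent and baseline (Discussion) | Yes | No |
| Scans read blind to arm (Image analysis) | Protects measurement, not entry | Protects measurement, not entry |
| Random effect for cohort (primary analysis) | Handles clustering, not a systematic difference between arms in who enters | Same |
| Adjustment for imbalance (primary analysis) | Optional, measured covariates only | Optional, measured covariates only |

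Nothing in the right-hand column stops the arms being selected differently. Frailty or motivation that is not recorded cannot be adjusted for.

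**Step 4: how large could it be?** The article gives no input for this, so what follows only shows scale. Suppose one arm holds an extra share *q* of a subgroup that was screened out of the other, and that subgroup's mean LV mass change differs by *D*. The spurious difference between arms is *q* × *D*.

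- *q* = 0.10, *D* = 10 g: 1 g, and 1/15 = 7 % of the 15 g target.
- *q* = 0.20, *D* = 20 g: 4 g, and 4/15 = 27 %.
- *q* = 0.30, *D* = 20 g: 6 g, and 6/15 = 40 %.

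All values of *q* and *D* are assumptions. The sign of *D* is unknown, so the bias could run either way.

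**The case against.** The strongest reply is that the article discloses the recruiter's knowledge and applies identical criteria to both arms, and that the risk is familiar in cluster trials. Cluster allocation was chosen to limit contamination of controls. Disclosure and common criteria do not show that the criteria will be applied alike. The cluster design can also be kept while eligibility is fixed earlier.

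Four further objections have force and limit the point.

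- **Most non-enrolment is not the recruiter's doing.** A reader might infer that most unit patients are filtered by someone who knows the arm. The article expects 80 % to meet the criteria and half of those to take part. The 50 % is mainly a decision by patients who have not been told their arm. The other 20 % also includes patients under three months on dialysis, those unable or unwilling to consent, and those who cannot be scanned. Exercise judgements are only part of it. By the article's own count, 130 of about 160 willing patients are needed (130/160 = 81 %), so discretion after consent is limited.
- **Fitness matters in both arms.** A reader might infer that the exercise exclusions have consequences only on a cycling shift. Controls do the same shuttle walk and sit-to-stand tests, so unfitness is relevant to them too.
- **The Discussion's claim is conditional.** It speaks of bias arising if patients are aware, and withholding the method from patients answers that. The claim is incomplete rather than false.
- **An article leaves operational detail to the full protocol.** The absence of a screening log is therefore no fault in itself. The fault is that the article names the recruiter's knowledge and then treats selection bias as a matter of patient awareness only.

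**Conclusion.** The point holds as a risk that the plan leaves open. Recruiters know the arm, at least one exclusion is a judgement about exercise, and the stated safeguards do not reach the recruiter. It rests on the possibility of uneven application; nothing in the article shows that this will happen.

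The size cannot be derived from the article. The 1 to 6 g range in the working rests wholly on assumed inputs.

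A reader might infer that sicker controls would bias LV mass change towards exercise. The article does not support that direction. If controls entered with higher LV mass and both arms regressed to a common mean, controls would fall more, which works against exercise. If each arm regressed to its own mean, a stable baseline difference need not bias a change score at all. Bias needs groups that would have changed differently, and the article does not say how they would. For function, quality of life and clinical events, a fitter exercise arm would plausibly look better, but that too is reasoning and not a figure from the article.

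This is a worthwhile, low-cost improvement to the plan. It does not invalidate the design.

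**What to change.** 1. **Units not yet allocated** (the Design section says the trial starts in three units, which leaves room for more). Complete eligibility screening, and consent where feasible, for both day-cohorts before the unit's shift allocation is drawn or revealed.
2. **Units already allocated.** Make and lock exclusion decisions for the whole unit list, under identical rules for both shifts, before anyone is approached. Then approach every eligible patient.
3. **All units.** Report numbers eligible, approached and consented by shift.
4. **Discussion.** State that withholding the method from patients addresses only the patient route, and that recruiter knowledge remains a possible source of selection bias.

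**Cost.** Screening is brought forward, and cycling starts somewhat later in new units. Completing all baseline cardiac MRI before allocation would be stronger still but should stay optional. Baseline assessments take place at one research centre, so waiting for a whole unit could delay starts and leave the earliest baselines out of date.
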